# Home-Based Intervention for the Prevention and Treatment of Malaria Among Children Younger Than 5 Years in the West Region of Cameroon: Protocol for a Randomized Controlled Trial

**DOI:** 10.2196/19633

**Published:** 2021-03-12

**Keywords:** home-based management, malaria, children younger than 5 years, home caregivers, West Region, Cameroon

## Abstract

**Background:**

Although malaria is preventable and curable, 1 child dies of this disease every 2 minutes in Africa. Home-based management of malaria reduces the progression of severe malaria by more than 50%. Scalable, efficacious, and cost-effective strategies are needed to empower the capacities of home caregivers of children younger than 5 years of age in health education, diagnosis, and treatment of malaria at home.

**Objective:**

The main objective of this trial is to assess the impact of the management provided by home caregivers on the prevention, diagnosis, and treatment of malaria in children younger than 5 years as compared to the home-based malaria management component of the integrated community-directed intervention (CDI) strategy of community health workers (CHWs).

**Methods:**

A randomized controlled trial will be conducted. CHWs have conducted a census of all households where there is at least one child younger than 5 years with their home caregivers. These children and their home caregivers have been randomly placed into the intervention or control groups among the households identified. The trial will allow malaria home-based prevention, diagnosis, and treatment of 350 children younger than 5 years old by home caregivers in the Fombap area (intervention group) where the integrated CDI strategy will not implemented. This group will be compared to the home-based malaria management component of the integrated CDI strategy in which 350 children in the same age group will be followed up by CHWs in the Baneghang area (control group). The primary outcomes will be the prevention, diagnosis, and treatment of malaria in children younger than 5 years of age by home caregivers at home. The secondary outcomes comprise the malaria follow-up indicators produced by home caregivers in the intervention group and those produced by CHWs in the control group. Both descriptive and one-way analysis of variance estimation techniques will be used to compare the mean difference in the 2 strategies.

**Results:**

From September 2019 to October 2019, all home caregivers with children younger than 5 years of age were identified in the intervention and control group by CHWs. Following this, 203 home caregivers with their 350 children younger than 5 years were randomly selected and enrolled in the intervention group, while 225 home caregivers with their 350 children younger than 5 years were enrolled in the control group. In the intervention group, 203 home caregivers were trained in November 2019. This home treatment effectively started in December 2019 and will continue until May 2020.

**Conclusions:**

Findings from this randomized controlled trial will contribute to resolving the challenges of severe malaria and to limiting the death due to malaria of children younger than 5 years. This will bring benefits to home caregivers who will know how to promptly diagnose and properly treat malaria in their children at home.

**Trial Registration:**

Pan African Clinical Trial Registry (PACTR) 202003487018009; https://pactr.samrc.ac.za/TrialDisplay.aspx?TrialID=9788

**International Registered Report Identifier (IRRID):**

DERR1-10.2196/19633

## Introduction

About 700,000 to 2.7 million people die of malaria each year, 75% of whom are African children [1]. There were also 435,000 malaria deaths worldwide in 2017, mostly in Africa, the majority being children younger than 5 years of age, with 1 child dying every 2 minutes from this preventable and curable disease [2]. In Africa, more than 70% of malaria cases in rural areas and more than 50% of cases in urban areas are self-treated, and formal health care is sought only if initial treatment fails [3]. According to World Malaria Report 2018, similar to the top 10 most affected African countries, Cameroon recorded an increase of about 131,000 additional cases of malaria compared to the previous year [2]. The report also revealed an insufficient level of access to resources and interventions for an effective fight against malaria [2].

Most parents go to street vendors rather than to the health care system for their medications. Many studies have shown that the majority of early treatments for childhood fever are given at home [4,5] and that these treatments are usually incorrect or suboptimal [6,7].

More than 90% of sick children in rural areas in Senegal receive their first treatment at home; unfortunately, most of the time, they receive inappropriate self-medication [8]. The majority of malaria cases are recorded in households rather than in health care facilities, as they are inaccessible to the majority of those with malaria. National surveys in the World Health Organization (WHO) African Region indicate that only about one-third of febrile children receive consultation from qualified health staff [9]. Early access to effective malaria treatment is one of the main strategies for reducing the burden of malaria. This means that treatment must be available and as close to the homes as possible within 24 hours from the onset of symptoms.

Home-based management of malaria (HMM) including diagnosis by rapid diagnosis test (RDT) and treatment based on test results is a promising strategy to improve the access of remote populations to prompt and effective management of uncomplicated malaria and to decrease mortality due to malaria [10]. It has been acknowledged that it is time to intensify the HMM in endemic countries to cover the majority of their populations, and that this will result in early access to good quality antimalarial drugs at appropriate doses within 24 hours from the onset of symptoms [10]. Accumulated experience shows that it is possible to improve malaria management in the household at the community level and to reduce morbidity and mortality [11].

Studies show that HMM reduces the progression of severe malaria by more than 50% and reduces the overall mortality of children younger than 5 years old by 40% [12,13]. It is now generally accepted that with appropriate training and use of prepackaged drugs, mothers can recognize fever and administer timely and appropriate treatment [12]. In the framework of successful programs, mothers, as primary home health caregivers for their children, have been trained in the early recognition of malaria symptoms and administration of appropriate treatment [12]. The ability of mothers or home caregivers to recognize malaria and administer prompt and appropriate treatment resulted in a 40% reduction in overall mortality in children younger than 5 years old in the program area [13].

In 2001, the WHO recommended an equity strategy aimed at improving access to essential care for children younger than 5 years old through the introduction of HMM [14]. In 2010, they recommended confirmation of diagnosis by microscopy or RDT before any treatment [15]. This ensures early recognition and prompt and appropriate response (treatment) to malarial illness in children younger than 5 years within the home or the community [14]. This strategy aims to enable home caregivers to recognize malaria early and respond appropriately, to ensure that home caregivers have adequate knowledge and capacity to respond to malaria, and to create an environment that enables the strategy to be implemented by making medicines available as near to the home as possible [14]. In Senegal, a pilot study on HMM conducted in 2008 demonstrated the feasibility of integrated use of RDTs and artemisinin-based combination therapy in isolated villages by volunteer home health caregivers [10]. HMM that includes RDT and treatment based on test results is a promising strategy for improving the access of isolated populations to an early and effective management of uncomplicated malaria and for reducing malaria mortality [10]. Home caregivers have demonstrated excellent adherence to guidelines, potentially contributing to a decrease in malaria-related deaths in the community [10].

Recently, successful introduction of RDTs into HMM programs has been reported in several African countries, including Cameroon [16,17]. However, the integrated community-directed intervention (CDI) strategy has only been implemented in some health districts in Cameroon. Thus, the interventions have not been made available, particularly for children younger than 5 years; yet, this age group constitutes a vulnerable population. Innovative interventions are needed at all levels, particularly concerning prompt and effective malaria management cases, a key strategy recommended by the WHO [18].

It is very strategic to use home caregivers (mothers of children for instance) for diagnosis and administration of antimalarial treatment because they are the ones who provide first aid to their children. Community health workers (CHWs) can supplement home caregivers in their work by providing more health education, resupplying household care kits, and seeking better access to medicines. Therefore, a strategy to train home caregivers on the diagnosis and administration of malaria treatment is particularly appropriate for achieving more complete coverage. The goals of the strategy are to ensure the early recognition and prompt and effective response to malaria at home, especially for children younger than 5 years old. This strategy will not only reduce the workload of CHWs, but will also solve the unavailability and distance problem that involves people having to walk to meet the CHW for treatment. The aim of the study is to investigate the impact of a home-based intervention strategy for the prevention, diagnosis, and treatment of malaria in children younger than 5 years. We hypothesize that an intervention aimed at empowering home caregivers can make the prevention, diagnosis, and treatment of malaria in children younger than 5 years at home better than those under the integrated CDI strategy of CHWs.

## Methods

### Study Area

This study will be community-based, occurring in 2 health areas of the West Region of Cameroon: the Fombap health area in Santchou Health District where the integrated CDI strategy will not be implemented (intervention group) and the Baneghang health area in Penka-Michel Health District where the integrated CDI strategy is being implemented (control group).

Figure 1 shows the multistage sampling approach, in which probability and nonprobability sampling methods were used to select the 2 health areas. 

**Figure 1 figure1:**
[figure not shown]
Flow chart of the sampling frame for the selection of 2 groups. CDI: community-directed intervention.

### Study Design

The study will use a randomized controlled trial design. The trial was registered with the Pan African Clinical Trial Registry (202003487018009) in South Africa on March 18, 2020. It will be a community-based study examining the impact and effectiveness of the home-based malaria prevention, diagnosis, and treatment of children younger than 5 years by home caregivers (intervention) as compared to the home-based malaria management component of the integrated CDI strategy of CHWs (control). Children younger than 5 years and their home caregivers have been randomly placed into the intervention and control groups after the completion of a census of all households in the area by CHWs. In the intervention group, home caregivers will be trained to perform the RDT and administer the treatment (artesunate-amodiaquine) to children younger than 5 years for prompt and effective management at home. CHWs will be responsible for providing health education and for supplying households with malaria kits. In the control group, children younger than 5 years will be followed up through the malaria indicators produced by CHWs.

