### Data Collection Procedure

Trained interviewers were blinded to group allocation and collected data using pretested questionnaires. For baseline data, a pretested questionnaire was administered to home caregivers on the perception (knowledge, attitudes, and practices) of malaria. This questionnaire will be repeated at the end of the intervention. During the intervention, a structured data collection form will be used and will contain monthly malaria follow-up indicators recorded by home caregivers in the intervention group and the malaria follow-up indicators recorded by CHWs in the control group. The data source for the study will be the malaria register used for the intervention in the Fombap health area and the malaria register used by the CHWs in the Baneghang health area.

In the experimental group (Fombap health area), 6 CHWs were chosen from the Fombap population of 5875 inhabitants, corresponding to 1 CHW per 1000 inhabitants. In each CHW’s zone, the CHW conducted a census of all the households where there is at least one child younger than 5 years and their home caregiver. From this census, children younger than 5 years old and their home caregivers were randomly selected for enrollment in the study. They will be trained in the prevention, diagnosis, and treatment of uncomplicated malaria at home. Malaria kits will be distributed to home caregivers to take care of the children younger than 5 years at home.

With Baneghang health area as the control group, 6 CHWs were also randomly selected from the 9 in the Baneghang health area. In each CHW’s zone, the CHW conducted a census in all the households where there is at least at least one child younger than 5 years and their home caregiver. After the households were identified, children younger than 5 years old and their home caregivers were randomly selected for enrollment in the study. Figure 2 shows the outline of the sampling method for the intervention.

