### The Control Group

The integrated CDI strategy is implemented in 5 health districts in the West Cameroon region, including the Penka-Michel Health District, from which our control health area, Baneghang, was randomly selected for the site of the control group. In this area, the malaria management component of the integrated CDI strategy is carried out by 9 CHWs, 6 of whom were randomly selected for the study. CHWs conducted a census in their respective zone of all the households where there is at least one child younger than 5 years and their home caregivers. After identifying the households, children younger than 5 years old and their home caregivers were randomly selected for enrollment in the study.

Usually, when there is a suspected case of malaria in the community, the patient is taken to the CHW's home. The patient is examined by the CHW to check for uncomplicated malaria. If the test is positive, the CHW conducts an RDT and administers malaria treatment; if the test is negative, the CHW refers these patients and those with severe malaria to the health care center and makes home visits to provide health education to parents.

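### The study is labelled a randomised controlled trial, but strategy was fixed by health area (one area per strategy); the random steps described are sampling, so strategy and area effects cannot be separated

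*Protocol article*

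**What the plan says.** The title, the abstract and the Discussion call the study a randomised controlled trial. Study Design says "The study will use a randomized controlled trial design" and that "home caregivers have been randomly placed into the intervention and control groups after the completion of a census". The Abstract (Methods) says the same of the children and their caregivers.

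The sections that describe what was done read differently:

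- **Study Area** locates the intervention group in "the Fombap health area in Santchou Health District where the integrated CDI strategy will not be implemented (intervention group") and the control group in "the Baneghang health area in Penka-Michel Health District where the integrated CDI strategy is being implemented (control group"). It adds that "probability and nonprobability sampling methods were used to select the 2 health areas".
- **Data Collection Procedure** describes a separate census in each area. For Fombap: "From this census, children younger than 5 years old and their home caregivers were randomly selected for enrollment in the study". The text for Baneghang is equivalent.
- **Step 2** and **The Control Group** repeat that the random draw was for enrolment. The Control Group also describes the districts running CDI, including Penka-Michel, "from which our control health area, Baneghang, was randomly selected for the site of the control group", and says that 6 of the 9 community health workers (CHWs) there were drawn at random.
- **Results** gives 350 of 715 children (203 of 408 caregivers) in the intervention area, and 350 of 708 children (225 of 451 caregivers) from the other census.

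Data Management and Analysis plans t tests and chi-square tests between the groups at P<.05. The Abstract (Conclusions) says: "Findings from this randomized controlled trial will contribute to resolving the challenges of severe malaria".

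**The concern.** Random allocation is what licenses a causal reading of a difference between groups. The article claims that property, but its procedures describe a different design. If strategy follows geography, any difference between the two areas can produce a difference in the indicators with no contribution from the strategy. Examples are transmission, access to care, wealth, net coverage, CHW quality and the existing CDI programme itself.

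The Introduction hypothesises that the caregiver strategy is better than CDI, and the Discussion says the findings will inform public health authorities. Readers who trust the label would credit the strategy with a difference that the design cannot attribute to it.

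**Working it through.** **1. The random steps, one by one.**

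| Random step described | Where | What it decides |
|---|---|---|
| Baneghang drawn as control site | The Control Group | Which CDI area is studied |
| 6 of 9 control CHWs drawn | Data Collection Procedure; Step 1; The Control Group | Which zones of Baneghang are studied |
| Children and caregivers drawn in Fombap | Data Collection Procedure; Step 2; Results | Who in Fombap is studied |
| Children and caregivers drawn in Baneghang | Data Collection Procedure; The Control Group; Results | Who in Baneghang is studied |

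None of these steps decides which strategy an area, household or child receives. No step is described by which a Fombap household could become a control or a Baneghang household could receive the intervention. No random assignment of strategy to area is stated.

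**2. Sampling fractions (Results).** Children: 350/715 = 49.0% and 350/708 = 49.4%. Caregivers: 203/408 = 49.8% and 225/451 = 49.9%. Each is a draw of about half from one area's own list, not a division of one common list between two strategies.

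**3. The plan's own sample size.** Inputs from Sample Size Calculation: p1 = 0.44, p2 = 0.33, z = 1.96 and 0.842, pooled p = (0.44 + 0.33)/2 = 0.385.

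- Pooled formula: n = [1.96·√(2 × 0.385 × 0.615) + 0.842·√(0.44 × 0.56 + 0.33 × 0.67)]² / 0.11² ≈ 306 per group.
- Unpooled formula: n = (0.2464 + 0.2211) × 2.802² / 0.0121 = 303.3 per group.
- The stated 300 is close to both. For 15% nonresponse, 300/0.85 = 353 and 300 × 1.15 = 345, so 350 is acceptable.

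The arithmetic is not at fault. It treats children as independent and has no term for area.

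**4. What two areas can show.** There is one area per strategy, so between-area variance has zero degrees of freedom. Strategy can be arranged over two areas in only 2 ways, so the smallest two-sided permutation p-value is 2/2 = 1.0. Enrolling more children in the same two areas changes neither fact.

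**5. Illustration under assumptions.** The article gives no between-area variance, so the area figures here are assumed.

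*Random area variation, no strategy effect.* At p = 0.385 and 350 per arm, SE = √(2 × 0.385 × 0.615/350) = 0.0368. If area means vary with SD s, the real rejection rate of the nominal 5% test is 2Φ(−1.96·SE/√(SE² + 2s²)):

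| Assumed s | Rejection rate |
|---|---|
| 2 points | 12% |
| 3 points | 20% |
| 5 points | 37% |

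*Fixed area difference of 8 points, no strategy effect (0.41 v 0.33, 350 per arm).* The null SE is √(2 × 0.37 × 0.63/350) = 0.0365 and the alternative SE is √((0.2419 + 0.2211)/350) = 0.0364. Then Φ((0.08 − 1.96 × 0.0365)/0.0364) ≈ 0.59, so the test is significant about 59% of the time.

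**The case against.** **Randomness was not confined to sampling within areas.** A reader might infer that only the draw of participants inside each area was random. The Control Group section does not support that, because Baneghang itself was randomly selected. The correction stands, but it does not rescue the label: drawing a control site from places already running CDI is sampling, not assignment of strategy.

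**The missing flow charts might show a random draw of areas.** Even if they did, there would still be one area per strategy, and the confounding would be just as complete.

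**The geography is disclosed.** The abstract and Study Area both name the two areas, so a reader should not infer concealment. The fault is the design label and the statement of random placement.

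**Some analysis could help.** The caregiver questionnaire is given at baseline and repeated at the end. For its outcomes, comparing changes between areas would remove stable area differences if trends were parallel. It would not remove area-specific changes, CDI was already running in Baneghang, and Data Collection Procedure describes no equivalent baseline for the register indicators. So it is too strong to say that no analysis can reduce the bias. What holds is that between-area variance cannot be estimated.

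**The planned comparison may not be unadjusted.** The article lists tests in condensed form, and an analysis plan that is not shown might add covariates. The point does not depend on this, because adjustment cannot turn assignment by area into randomisation.

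**The rejection rates have no source in the documents.** This is correct. They show sensitivity and do not measure this trial's bias.

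**Conclusion.** The point holds and needs correcting. The article claims random allocation, and its own Study Area, Data Collection Procedure, Step 2, Control Group and Results sections describe assignment by health area. Strategy and area are completely confounded, so a significant between-group test cannot be attributed to the strategy.

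This follows from the text alone and does not depend on the illustrative figures (12%, 20% or 37% false rejection for assumed SDs of 2, 3 or 5 points; about 59% for an assumed 8-point area difference). A reader might take those figures as evidence that the result will be biased by a known amount or in a known direction. The documents support neither.

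**What to change.** - Remove the randomised-trial label and the statement of random placement from the title, abstract, Study Design, Discussion and conclusions.
- Describe a non-randomised controlled comparison of two health areas, with random sampling of children and caregivers within each area. State how each area was chosen.
- Limit the conclusion to an association between strategy and indicators, and state that area and strategy effects cannot be separated.
- A model adjusted for child age, caregiver age and number of children under 5 may be added as a supporting analysis. These covariates do not capture transmission, access to care, wealth, net coverage or CHW quality, so the model must not be presented as removing the confounding.
- Correct the registry entry if it describes random allocation. That record was not available for this review.

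The cost is rewording and, if wanted, one extra model. No further participants are needed and nothing in the conduct of the study changes. The downside is that the study can no longer be called randomised.
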